As part of the mDOT, patients will be given verbal and written material about the toxicities associated with each medication including ABC. The educational material will give specific information about ABC HSR. This information will describe the early signs and symptoms of HSR and the risk of continuing with ABC in the face of these symptoms. Patients will be instructed to contact the study personnel using the 24 hour per day telephone service or present to the clinic immediately. The patients will be told that a study doctor will make the decision to stop the medication, but it is their responsibility to notify the study doctors of the signs and symptoms of ABC HSR. Patients will be instructed that they may not take ABC at any time in the future if ABC HSR occurs. This counseling will be done by study personnel who are fully knowledgeable about the risks of antiretroviral therapy, especially ABC. All patients will be given a card that indicates that they are receiving ABC as part of this study. The card contains instruction for how to reach a study doctor. It will also instruct health care providers to notify study personnel regarding the health of the patient.

## 5.3 Post Outcome – Step 3

During the study period, patients in Step 2 may develop a primary study outcome. If this event happens, the outcome will be confirmed and patients will be evaluated for safety of starting antiretroviral therapy. Patients who have experienced the main study outcome and who are eligible to start antiretroviral therapy will enter Step 3. For patients with a primary outcome but not eligible for antiretroviral therapy, because of contraindications to starting ARV treatment, they will remain in Step 2 and have the safety assessments repeated monthly or as clinically indicated until they are found eligible for antiretroviral treatment.

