Patients will be assessed for the primary study outcome when CD4+ count falls below 250/ml or upon the development of a WHO stage IV AIDS-defining condition or a definitive diagnosis of a severe bacterial infection that meets WHO Stage 3 classification (Appendix II). To confirm the CD4 outcome, the CD4+ cell count will be repeated within 1 month after the initial measure below 250. If two measurements are <250 cells/L within a 3month time period, then the primary outcome has been confirmed. The outcome of an AIDS-defining condition must be confirmed by definitive or presumptive criteria (Appendix II). To confirm the outcome the following will be performed (see Appendix I, Step 3):

1. Medical history and physical examination, including weight
2. Adverse Event Survey
3. New diagnosis and hospitalization survey
4. Pregnancy test (urine or serum)
5. CD4+ lymphocyte count
6. CBC with differential
7. Liver function tests (AST and serum bilirubin)
8. Serum creatinine
9. Disease specific diagnostic test

These results will be valid for a period of two weeks and may be used for the safety evaluation, if within the acceptable range and time frame (2 weeks).

While the primary outcome is being confirmed patients will also be undergoing a pre-ARV safety assessment. If the evaluations below were not previously within the acceptable range or outside the two week time frame the evaluation that was not acceptable will be repeated. This ARV safety assessment may include results from the following (see Appendix I, Step 3):

1. Medical history and physical examination, including weight
2. Adverse Event Survey
3. New diagnosis and hospitalization survey
4. Pregnancy test (urine or serum)*
5. Complete blood count with differential
6. Liver function tests (AST and serum bilirubin)
7. Serum creatinine

**for those subjects that produce a positive pregnancy test see section 8.3 for specific ARV therapy assignment*

These results will be valid for a period of two weeks and will be used to determine whether there are any contraindications to starting antiretroviral therapy The following are relative contraindications to starting antiretroviral therapy for patients participating in this study (see section 4.4):

1. Fever > 38.0˚ C;
2. Weight < 40 Kg;
3. AST > 2.0 times upper limit of normal;
4. Creatinine > 2 mg/dL;
5. Hemoglobin < 9.5 g/dL;
6. Absolute neutrophil count < 1000 cells;
7. Current treatment with Ribavirin or Doxorubicin

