# 6.0 STUDY OUTCOMES

The main outcome of the study will be progression of HIV disease (Table 6). The time of the main outcome will be defined as the interval from enrollment until an outcome event first occurs. In the case of CD4+ counts, when a subject has met the criteria for primary outcome, the date of the first of two CD4+ counts < 250/ml will be used. Secondary outcomes will be response to antituberculosis therapy and safety.

For analysis, a Clinical Review Committee, chaired by the PI or designee, will be formed at the start of the study to review and classify all outcomes of the trial in a blinded way. Outcomes will be recorded on standard data collection forms for entry into an outcomes database. For clinical care on-site, medical officers will operationalize outcome definitions so that patients may be treated in a timely manner.

Table 6. Summary of Study Outcomes

| Study Aim | | Measurement |
| --- | --- | --- |
| Primary Objective | Aim |
| HIV Disease Progression | 1 | Time interval from enrollment until 2 CD4+ count < 250/*µ*L within a 3 month time period , rate of decline in CD4+ T cell counts  - Development of AIDS-defining condition (WHO Staging System; not including recurrent TB)  - Definitive diagnosis of a severe bacterial infection that meets WHO Stage 3 criteria  - Death |
| Secondary Objectives |  |  |
| Response to Antituberculous therapy  Safety | 2  3 | MTB Sputum Conversion  Cure of active TB  TB Treatment failure  TB Relapse  Grade III/IV adverse reactions  Paradoxical reactions  HIV Drug resistance |

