### **7.4.2 Post- Primary Outcome - Antiretroviral Therapy Follow-up Visits**

Prior to being started on self-administered ARV therapy and entry to STEP 3, a pre-ARV baseline evaluation will be completed; this will include the following examination (appendix I, Step 3):

1. HIV RNA Roche Amplicor
2. Quality of life assessment
3. Plasma storage
4. PBMC storage/ immune function (Flow cytometry to assess cell surface activation markers, EliSpot to assess CD4 and CD8 T cell specificity to HIV and microbial peptides, Whole blood assays to determine antigen specific response to HIV and microbial antigens)

Assessments from confirmation of study outcome, or ARV safety evaluation may be used for pre-antiretroviral baseline if they were completed within two weeks before ARV baseline.

Patients will then be started on self-administered, ARV therapy and enter STEP 3 (Section 5.0 describing the initiation of therapy). Patients will receive detailed counseling about treatment with antiretroviral therapy. They will be informed that adherence measures will be made including unannounced home visits to record self-reported adherence and pill counts. Below is the schedule for STEP 3:

1. Medical history and physical examination including weight (Week 2, months 1, 2, 3, 6, 9, 12, 15, 18, 21, 24, 27, 30, 33, 36, and then every 4 months or as clinically indicated)
2. Adverse experiences survey (Week 2, months 1, 2, 3, 6, 9, 12, 15, 18, 21, 24, 27, 30, 33, 36, and then every 4 months or as clinically indicated)
3. New diagnoses and/or hospitalizations since the last study visit (Week 2, months 1, 2, 3, 6, 9, 12, 15, 18, 21, 24, 27, 30, 33, 36, and then every 4 months or as clinically indicated)
4. Urine or serum -HCG pregnancy test (if suspect)
5. CD4+ lymphocyte count (months 3, 6, 12, 18, 24, 30, 36, then every 4 months thereafter or as clinically indicated)
6. CBC with differential and platelet count (months 3, 6, 12, 18, 24, 30, 36, then every 4 months thereafter or as clinically indicated)
7. Posterior-anterior chest X-ray (as clinically indicated)
8. Sputum semi-quantitative AFB smear and culture on solid media X 2 (as clinically indicated)
9. MTB drug susceptibility (as clinically indicated)
10. Serum aspartate aminotransferase (AST), serum bilirubin (months 1, 2, 6, 12, 18, 24, 30, 36, and every 4 months thereafter or as clinically indicated)
11. Serum creatinine (as clinically indicated)

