The main objective of this analysis is to determine whether punctuated ARV given during TB jeopardizes the response to continuous ARV therapy when given to participants who develop CD4+ count < 250/µL. In this analysis, there are 3 major outcomes of interest: CD4+ response, viral dynamics, and viral resistance to ARVs. Safety in terms of toxicity will also be evaluated. In terms of the CD4+ response, we will extend the linear spline model to include another knot, t**, at the time when an individual reaches CD4+ count < 250/µL. This modification of the model will allow us to compare the slope among patients who received punctuated therapy and those who did not. Viral dynamics, viral resistance and safety will be analyzed.

Ancillary Analyses

*Immunologic and Viral Dynamics (see appendix X.)*

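### The CD4+ response to continuous ARV is measured from the first count below 250/µL instead of from the start of ARV, so untreated decline is fitted as part of the on-treatment slope

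*Protocol*

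**What the plan says.** The analysis stands in Section 10.2.2.3 under the additional outcomes. It asks whether punctuated ARV "jeopardizes the response to continuous ARV therapy when given to participants who develop CD4+ count < 250/µL". It names three outcomes: "there are 3 major outcomes of interest: CD4+ response, viral dynamics, and viral resistance to ARVs". For the first, the linear spline is extended "to include another knot, t, at the time when an individual reaches CD4+ count" below 250/µL, and the slopes of patients with and without earlier punctuated therapy are then compared.

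The date of that event is fixed elsewhere. Section 6.0 states that "the date of the first of two CD4+ counts < 250/ml will be used"; Sections 6.1.1 and 10.2.2.1 agree. In Section 10.2.2.1, period 2 of the spline also ends when CD4+ falls below 250/µL.

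ARV starts later. Section 5.2 requires two counts below 250/µL within three months. Under Section 5.3, "the CD4+ cell count will be repeated within 1 month after the initial measure below 250". Patients who reach the outcome but have contraindications do not start: "they will remain in Step 2 and have the safety assessments repeated monthly or as clinically indicated until they are found eligible".

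**The concern.** The question concerns response to treatment, but the clock starts at an event that comes before treatment. Apart from a patient still on punctuated ARV at the event, anyone who qualifies by CD4+ spends some time untreated after the knot. Because period 2 has already ended, the decline in that interval is assigned to the segment that is read as the response to ARV.

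This has three consequences. The on-ARV slope is too low in each arm. If the gap is the same in both arms, a real difference between them is shrunk, which works against detecting the harm that this analysis is meant to find. If the gap differs, part of the slope difference reflects time to ARV start and not response.

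The protocol already has the appropriate origin. Section 5.3 defines formal entry to Step 3 with a pre-ARV baseline, the Appendix I Step 3 schedule marks the start of ARV, and virologic failure is timed by months of therapy (Sections 8.1.3 and 10.2.2.3).

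**Working it through.** The protocol gives no figure for this analysis, so there is nothing to reproduce. The check asks what slope the planned model returns when the true slope is known.

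**Inputs from the protocol**
- Untreated decline: 7 to 10 cells/month (Section 10.1); the midpoint, 8.5, is used.
- Gap g from first low count to ARV: about 1 month as planned, since the repeat is due within a month. The pair may span 3 months, and contraindications can add more.
- Step 3 counts (Section 7.4.2): "CD4+ lymphocyte count (months 3, 6, 12, 18, 24, 30, 36, then every 4 months thereafter or as clinically indicated".

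**Assumptions not in the protocol**
- A straight-line rise on ARV of 15 cells/month, varied to 5 and 10.
- Pre-event counts at −12, −9, −6, −3 and 0 months; one repeat at 1 month; no measurement error.

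**Untreated decline after the knot** = rate × g: 7 to 10 cells for g = 1, and 21 to 30 cells for g = 3.

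**Fitted slope.** With u in months from the first low count, the true course is 250 − 8.5·min(u, g) + 15·max(u − g, 0). The planned model, a + b1·min(u, 0) + b2·max(u, 0), is fitted by least squares, and b2 is read as the response.

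| Step 3 counts to month | b2, g = 1 | b2, g = 2 | False difference, 1 v 2 months |
|---|---|---|---|
| 6 | 12.1 | 9.1 | 3.0 |
| 12 | 13.6 | 11.8 | 1.9 |
| 24 | 14.4 | 13.5 | 0.9 |

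The last column is taken before rounding (for month 12, 13.61 − 11.75 = 1.86). With the knot at ARV start the fit returns 15.0 exactly.

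**Hand check.** The straight line from the first low count to Step 3 month p has slope (−8.5g + 15p)/(g + p). For g = 1: p = 6 gives 81.5/7 = 11.6, p = 12 gives 171.5/13 = 13.2, and p = 24 gives 351.5/25 = 14.1. These agree closely with the fits.

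**Other true slopes, counts to month 12.** A true +5 is fitted as 4.2 (g = 1) or 2.2 (g = 3); a true +10 as 8.9 or 6.1.

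**Dilution with equal gaps, counts to month 12.** A true difference of 3 cells/month (10 v 7) becomes 2.8 (g = 1) or 2.4 (g = 3).

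**Clinical-event starters.** ARV also starts on a WHO stage IV condition or a definitive severe bacterial infection, whatever the CD4+ count (Section 5.2). If CD4+ is still 250 or more, the event that ends period 2 has not occurred, so as written these patients' on-ARV counts stay in period 2.

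**The case against.** The best defence is that the planned wait is short. Sections 5.3 and 7.4.1 run the pre-ARV safety assessment while the outcome is being confirmed, so it adds no separate stage. The listed contraindications are called relative, and persistent abnormalities attributed to HIV do not bar ARV. CD4+ is measured to month 36 and beyond, and the error shrinks with follow-up: for a one-month gap it falls from 19% of the true slope with counts to month 6 (2.9/15) to 4% with counts to month 24 (0.6/15). All of this stands and limits the size. It does not remove the error, because the confirming count always comes after the knot, and patients who progress late will have short Step 3 follow-up.

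Three stronger readings are tempting and are not supported:
- **That the arm comparison is known to be biased in one direction.** The same Step 3 rules apply to both arms. Earlier zidovudine exposure could plausibly make waits unequal through anaemia or neutropenia, but the protocol gives no evidence that it does.
- **That clinical-event starters with CD4+ of 250 or more are wrongly dropped.** The heading and objective limit this analysis to participants whose CD4+ falls below 250/µL, so these patients are outside its stated scope. What remains is that their period 2 has no proper end.
- **That the trial's answer on later treatment is undermined.** CD4+ response is one of three outcomes in an additional analysis. Virologic failure is timed from therapy, and the primary endpoint is untouched.

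**Conclusion.** The point holds for the CD4+ outcome of this one additional analysis. Followed as written, the plan fits untreated decline as response to ARV. That the slope is understated does not depend on the assumed figures, provided CD4+ falls before ARV and rises on it; the size does.

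At the planned gap of about one month and a true rise of 15 cells/month, the understatement is about 2.9, 1.4 or 0.6 cells/month with Step 3 counts to month 6, 12 or 24. A two-month gap makes it about 5.9, 3.2 or 1.5. A false difference of 3.0, 1.9 or 0.9 cells/month arises only if one arm waits one month and the other two. Longer gaps give larger errors, but the protocol states no frequency for them, so they should not be taken as typical. This should be corrected; it does not threaten the main result.

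**What to change.** In Section 10.2.2.3, define the added knot as the date of the first Step 3 ARV dose. In Section 10.2.2.1, end period 2 at that date, or model the interval from the event to ARV start as its own segment. Report that interval by arm.

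For patients who start ARV on a clinical event with CD4+ of 250 or more, also end period 2 at ARV start, and state whether they enter the response comparison.

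State that Step 3 entrants are a post-randomization subset. Do not adjust the main comparison for pre-ARV CD4+, pre-ARV viral load or Step 3 regimen: punctuated ARV may itself alter all three, and adjustment could remove the harm under test. At most, use them in a labelled sensitivity analysis.

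The cost is that the model needs the ARV start date, which the Step 3 schedule already marks, and one re-specified segment. No visit, test or treatment rule changes.

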**Patients Ineligible for Intervention after 4 weeks of TB Treatment**

Patients who have persistent contraindications to starting ARV therapy after 4 weeks in Step 1 will remain in the study. Patients in this group are followed because of our ethical obligation to them after enrolling them in the study. These patients will be treated for active tuberculosis and monitored for primary study outcomes according to the schedule for assessments outlined in Step 2. These patients will be registered to Step 2 but will not be randomized nor will they be included in the primary analysis of the study. They will be eligible for entry into Step 3 of the study if, during the study period, their CD4 count drops below 250/ml or an AIDS- defining condition develops as defined by WHO stage IV HIV infections or a definitive diagnosis of a severe bacterial infection that meets WHO Stage 3 classification (Appendix II)

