In addition to the main outcome, we will determine whether the study interventions alter the rate of decline in CD4+ counts by using a linear spline model with 2 time periods. The follow-up period will be divided into two periods: period 1 - from baseline until 6 months; period 2 - from 6 months until CD4+ count falls below 250/µL. Separate slope parameters will be fit for period 1 and period 2 using the linear spline model with a knot, t*, at 6 months. This approach will allow us 1) to analyze the magnitude of effect achieved during the punctuated treatment during period 1 and 2) to compare the rates of decline for the different treatment groups in period 2. The general model is given by:

where yij is the CD4+ count for subject i (i = 1,2, … n) and measurement j (j = 1, 2, … m), G represents the two mutually exclusive treatment groups (punctuated ARV vs. reference group), and t* = 6 months on study. Using appropriate contrasts, we can test for differences in **11G between the groups assigned to punctuated therapy or delayed therapy for period 1. In this analysis, the main interest is not whether there will be a difference in CD4+ slope between the treated and delayed group, but instead what is the magnitude of the difference. This information will be useful in analyzing the response during period 2. Again using appropriate contrasts, we will compare the slopes of the two treatment groups during period 2. The null hypothesis for this analysis is: **2Punct ARV = **2Delay ARV;; the alternative hypothesis is that the two groups will have different slopes in CD4+ measurement. To perform this analysis, we will use the linear mixed-effects model.85

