#### **10.2.2.2 Specific Aim 2**

To determine whether a punctuated six-month course of ARV therapy during treatment of active TB will improve the response to antituberculous therapy, as measured by one month culture conversion, treatment failure, and relapse TB, among patients with active TB and CD4+ cell count above 350 cells/µL.

The analysis of this Specific Aim will include only patients with active TB that have been randomized in the clinical trial. The effect of ARV treatment on the response to antituberculous therapy will be evaluated by comparing the proportion of subjects with negative smears or cultures at one and two months (chi square test). A similar analysis will be performed for antituberculosis treatment failure in the ARV treatment arms compared to the reference arm.

Previous published studies of TB in HIV infection estimate relapse rates between 3 and 10%; we thus expect to identify between 10 to 35 relapse cases of TB during the study. The cumulative incidence of TB relapse will be estimated by group using Kaplan-Meier methods; incidence density methods will also be used to measure the number of relapses per 100 person-years of observation after completing antituberculous treatment according to ARV treatment group. The incidence density ratio (95% confidence interval) will be estimated to compare incidence in treated and reference groups. Cox regression analysis will be used to determine whether punctuated ARV therapy is associated with relapse after adjusting for covariates. The analysis will account for the different treatment histories by using time-dependent Cox proportional hazards analysis. The analysis will be further stratified according to relapses due to reactivation and reinfection based on the RFLP patterns.

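### The test of whether punctuated ARV harms later ARV response compares progressors by therapy received, does not exclude never-randomized patients, and is not labelled as non-randomized

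*Protocol*

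**What the plan says.** The subsection of 10.2.2.3 on patients whose CD4+ count has fallen below 250 and who begin continuous ARV has a causal aim: whether punctuated therapy "jeopardizes the response to continuous ARV therapy when given to participants who develop CD4+ count" below that level. For the CD4+ response, "we will extend the linear spline model to include another knot", placed at the time the patient crosses the threshold, in order to "compare the slope among patients who received punctuated therapy and those who did not".

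Other sections bear on who is compared:

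- Section 5.2.1.1, on patients still ineligible after 4 weeks of TB treatment, says that they "will not be randomized nor will they be included in the primary analysis of the study". It adds: "They will be eligible for entry into Step 3 of the study", on the same triggers as everyone else. Section 5.2.2 repeats both points.
- Section 10.2.2.2 limits its population: "The analysis of this Specific Aim will include only patients with active TB that have been randomized in the clinical trial". Section 10.2.2.3 has no such sentence.
- Section 10.2.2.1 applies the as-assigned rule to the main analysis of Aim 1, and Section 10.2.2.4 ties intention to treat to the primary analysis.
- In the spline being extended (Section 10.2.2.1), "G represents the two mutually exclusive treatment groups (punctuated ARV vs. reference group"), and one of its contrasts is "between the groups assigned to punctuated therapy or delayed therapy for period 1".
- Section 5.2 states that patients without a study outcome do not enter Step 3.

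**The concern.** There are three separate weaknesses.

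1. **Receipt instead of assignment.** Taken literally, a patient assigned to punctuated therapy who did not take it would move to the comparator.
2. **An open population.** A never-randomized patient who progresses has not received punctuated therapy, so the literal wording fits that patient too. These patients had contraindications that persisted to week 4, such as fever, low hemoglobin, raised AST or low weight (Section 4.4), and they are not exchangeable with the randomized reference arm.
3. **Selection on the primary outcome.** Progression happens after randomization and is the event the intervention is meant to delay. Patients who progress despite punctuated therapy may differ from those who progress without it. Assigning everyone correctly does not remove this.

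Section 1.1.2 raises resistance after a planned interruption as a concern, and the Step 3 schedule in Appendix I describes that follow-up as serving the secondary objectives of safety and ARV resistance. A difference in later response, or the lack of one, will be read as evidence on whether the strategy costs patients something later. The plan poses that causal question without saying that the comparison is unprotected, and names no adjustment for it.

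**Working it through.** The plan gives no sample size, power or alpha for this comparison, so there is no figure of its own to reproduce. Two quantities can be sized.

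**Share of each arm that progresses**

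Inputs from Section 10.1 and the Figure 5 legend: effect size 35%, read here as a hazard ratio of 0.65 (the formula did not survive in the text); constant hazard; 3-year accrual; 5% dropout per year; 50% progression in the reference group by 2 or by 3 years; 175 per arm. The synopsis gives a 5-year study with at least 2 years of follow-up, so follow-up is taken as uniform on 2 to 5 years.

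With progression hazard λ, dropout hazard δ = −ln(0.95) = 0.0513 and h = λ + δ:

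P(progress) = (λ/h) × {1 − [exp(−2h) − exp(−5h)] / (3h)}

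| Scenario | Arm | λ per year | P(progress) | of 175 |
|---|---|---|---|---|
| 50% by 2 years | Reference | ln 2 / 2 = 0.3466 | 0.642 | 112 |
| 50% by 2 years | Punctuated | 0.65 × 0.3466 = 0.2253 | 0.496 | 87 |
| 50% by 3 years | Reference | ln 2 / 3 = 0.2310 | 0.505 | 88 |
| 50% by 3 years | Punctuated | 0.65 × 0.2310 = 0.1502 | 0.372 | 65 |

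These are shares reaching the outcome. Deaths and persistent contraindications would lower the numbers who start ARV.

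**How unlike the two sets of progressors are**

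This needs an assumption about unmeasured risk. Each patient was given a log-normal frailty on the progression hazard (SD 0.5 or 1.0, assumed), with the same accrual, dropout and hazard ratio and no true effect on later response.

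| Scenario, frailty SD | Excess frailty of punctuated-arm progressors | Mean time to progression, reference vs punctuated (years) | Mean follow-up after progression (years) |
|---|---|---|---|
| 2 years, 0.5 | 0.063 SD | 1.30 vs 1.44 | 2.13 vs 2.03 |
| 2 years, 1.0 | 0.091 SD | 1.17 vs 1.29 | 2.24 vs 2.14 |
| 3 years, 0.5 | 0.051 SD | 1.44 vs 1.54 | 2.04 vs 1.96 |
| 3 years, 1.0 | 0.089 SD | 1.28 vs 1.39 | 2.15 vs 2.07 |

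A different model gives a larger gap. Take linear CD4+ decline of mean 8.5 cells/month (SD 4, assumed) from an assumed entry distribution centred near 500, follow-up of 24 to 60 months, and an imposed 12-month delay, which is the average delay Section 10.1 names. Then about 64% and 46% progress, with about 20 and 14 months of follow-up afterwards. The imbalance is therefore model-dependent.

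**Never-randomized patients, if they were counted**

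The protocol gives no number for them. If k such patients progressed at the reference-arm rate, their share of the comparator would be k/(175 + k). For assumed k = 17, 35 and 70 this is 17/192 = 9%, 35/210 = 17% and 70/245 = 29%. This shows what leaving the population open could cost; it is not an estimate of what will happen.

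**The case against.** The strongest reply is that the wording is shorthand. Section 10.2.2.3 creates no new grouping. It extends a spline whose group term is the two trial groups, with a contrast described by assignment, and the rest of the section compares study arms or the two strategies. Never-randomized patients belong to neither arm, are followed out of ethical obligation (Section 5.2.1.1) and are outside the sample size (Section 10.1). This stands in part: a reader might infer that the plan admits these patients to the comparator, and the documents do not support that. They leave the point open, and the express limit in Aim 2 makes its absence here noticeable.

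A reader might also infer that the flaw would hide harm. That is not supported either. Sicker never-randomized patients could make the comparator look worse, but nothing in the protocol shows that a week-4 contraindication predicts a poorer CD4+ response on ARV much later. Selection of frailer progressors in the punctuated arm would push the other way. Directly observed dosing (Section 5.2.4) limits non-receipt, and the mixed model tolerates unequal follow-up.

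Finally, a question about response among those who start ARV must condition on starting it, and this is an additional-outcome analysis that nowhere claims to be randomized. That is fair. It is a reason to label the analysis and adjust it, not to drop it. It does not answer the receipt wording or the selection on progression.

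**Conclusion.** The point holds in a limited form. The stated contrast is by receipt, the population does not exclude never-randomized patients, and conditioning on progression means that randomization does not protect the comparison, even by assigned arm. Under the protocol's design assumptions, with the effect read as a hazard ratio of 0.65, the arms would contribute about 64% and 50% of their patients, or 51% and 37%.

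How much bias follows is not settled. In the constant-hazard frailty model it is modest: 0.05 to 0.09 SD in frailty and about 0.1 year in follow-up. With an imposed 12-month delay the follow-up gap is larger. The net direction is unknown. Any contamination by never-randomized patients rests on an assumed number.

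The primary intention-to-treat analysis is unaffected. This is a cheap improvement to a safety-related additional analysis, not a threat to the trial's main result.

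**What to change.** In Section 10.2.2.3:

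- Restrict the analysis to randomized patients and compare by assigned arm.
- Adjust for prognostic factors already collected before randomization: screening CD4+ count and baseline HIV RNA.
- Add a sensitivity analysis that also adjusts for status at Step 3 entry (CD4+ count, HIV RNA) and time since randomization. It should not be the main version, because punctuated therapy may itself change these variables.
- State that the result is conditional on progression and not protected by randomization.

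An all-randomized comparison at a fixed time, such as month 24, may be added as supportive, with its components shown separately. It should not replace the Step 3 analysis. Counting event-free patients off ARV as successes mixes the efficacy benefit into a safety test. As an illustration, take 64% and 50% progressing, assumed suppression on ARV of 85% and 75%, and no deaths. Success is then 0.36 + 0.64 × 0.85 = 90.4% in the reference arm and 0.50 + 0.50 × 0.75 = 87.5% in the punctuated arm. A 10-point loss of suppression appears as about 3 points. A visit window would also be needed, because Step 3 visits are timed from the start of ARV.

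The cost is a few sentences, some extra analysis and a weaker causal statement. The restriction, the arm comparison and the adjustment need no new data.
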